### Sample size calculation and recruitment

The sample size was calculated by assuming p < 0.05 as the significance level, 80% power and 1 to 1 as the ratio of unexposed to expose in sample. The calculation was carried by using the OpenEpi version 2.3.1 [15]. On the assumption of an SD of 15 mmHg and 30% drop out, a sample size of 160 participants per group is required to detect the effect size of systolic blood pressure 5.4 mm Hg. The effect size used to calculate the sample size was based onthe result of a previous similar study[16].

Universal sampling method will be used to recruit the study participants. The 431 residents of the selected community housing complexes who were diagnosed as (stage 1 to 3) hypertension will be invited to the study. We will take all participants which fit with inclusion criteria and willing to participate to the study so that actual participants may be more than calculated sample size.

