### Follow up and outcome measurement

The follow up will be at six months and twelve months for both intervention and control groups. The GPAQ questionnaire survey, 7 days diet history, blood pressure measurement and physical evaluation will be conducted at baseline, six months and twelve months. The log book kept by participants in the intervention group will be checked for completeness and errors after one month of the intervention and the record will be taken at three, six, nine and twelve months in order to check the compliance of self-blood pressure monitoring and home-based exercise, and whether they measured their blood pressured once a week or not.

The primary outcomes will be systolic and diastolic blood pressure measured at zero month (enrolment), six months (end of intervention period), and twelve months (maintenance period). Secondary outcome measures include some Social Cognitive Theory variables related to self-efficacy and self-regulatory such as practice of self-blood pressure monitoring, and adherence of exercise. Other secondary outcomes will be dietary intake, level of physical activity and physical fitness in term of both cardio vascular endurance and muscle strength.

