### Data management and analysis

The data analysis will be done by using Stata software (version 11: StataCorp). Bivariate analysis such as Chi-square tests (for dichotomous and categorical variables), t test and ANOVA (for continuous and normally distributed variables) and Mann-Whitney-U test (for continuous variable with skewed distribution) will be applied to compare the two groups with respect of socio-demographic characteristics, number of clinic visits, practice of self-blood pressure monitoring, blood pressure at the time of enrolment, dietary intake, level of physical activity and fitness.

The primary outcome, change in systolic and diastolic blood pressure at six months and twelve months will be compared between and within the groups by using t test and ANOVA. If there are some differences in group characteristics, it will be adjusted by performing multivariate analysis of variance (MANOVA).

Since the secondary outcomes such as numbers of self-blood pressure monitoring, dietary intake, body composition (BMI, fat percentage, waist and hip circumference ratio), level of physical activity and physical fitness are also continuous variables, these will be examined as per primary outcome. The normality of the continuous variables will be checked before analysis and proper transformation will be done if the data is not normally distributed. The level of statistical significance will be set at p < 0.05.

In order to calculate nutrient intake, Nutritionist Pro™ Diet Analysis software will be used to analyse the diet record. It will focus mainly on energy, protein, fat, carbohydrate, sodium, dietary fibre and others. Based on the 7 days diet histories, the average energy consumed with macronutrients (e.g: Energy intake (kcal), protein (g), fat (g), saturated fat (g) and others) and micronutrients (e.g: calcium (mg), iron (mg), vitamins and minerals) value will be calculated. All nutrient intakes will be transferred to the Stata software for final data analysis.

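### Adjustment of the blood pressure comparison is decided after the data are seen, with no criterion and by MANOVA; baseline pressure should be a covariate in every analysis

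*Protocol article*

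**What the plan says.** All of the following is in the protocol article.

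- Data management and analysis defines the main comparison as "The primary outcome, change in systolic and diastolic blood pressure at six months and twelve months", tested both between and within the arms by t test and ANOVA. No covariate is named.
- The same section first compares the arms on a list of characteristics that includes enrolment blood pressure. It then gives the adjustment rule: "If there are some differences in group characteristics, it will be adjusted by performing multivariate analysis of variance (MANOVA".
- Follow up and outcome measurement shows that the data for a standing adjustment exist: "The GPAQ questionnaire survey, 7 days diet history, blood pressure measurement and physical evaluation will be conducted at baseline, six months and twelve months".
- Sample size calculation and recruitment sizes the trial on a difference in mmHg: "a sample size of 160 participants per group is required to detect the effect size of systolic blood pressure 5.4 mm Hg".

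These are stated rules, not details left to an analysis plan that is not shown.

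**The concern.** Three features of the stated analysis cause difficulty.

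1. **The trigger is open.** Nothing says what counts as a difference, which characteristics would then enter the model, or whether the adjusted or unadjusted result is primary. The model is chosen with the data in hand.
2. **The named method does not do the job.** MANOVA tests several outcomes together. Adjustment needs covariates (ANCOVA, MANCOVA or a mixed model). The omnibus test also does not give the quantity on which the trial was sized, a difference in mmHg with a confidence interval.
3. **The default gives up precision.** A change score subtracts baseline pressure with a slope fixed at 1, whereas a model with baseline as a covariate estimates that slope.

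In addition, within-arm tests stand beside the between-arm test with no order of importance. A within-arm change has no concurrent control, so it also contains any calendar effect.

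**Working it through.** **Inputs from the article.** Two-sided alpha 0.05 (sidedness is not stated; only two-sided reproduces the sample size), 80% power, 1:1 allocation, SD 15 mmHg, difference 5.4 mmHg, 30% dropout, four complexes with two per arm.

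**Assumed, because the article gives no figure.** Baseline-to-follow-up correlation r, mainly 0.5–0.7 with 0.3–0.8 shown; ICC of change 0.02–0.05.

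**Step 1: the plan's own figure.** n = 2(1.96 + 0.84)² × 15² / 5.4² gives 122 evaluable per arm. 122 × 1.3 = 159, which matches the stated 160. After 30% loss, 160 × 0.7 = 112 per arm remain, with about 77% power at SD 15.

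**Step 2: precision for independent participants.** With s the SD of a single reading:
- change score: variance 2(1 − r)s²
- baseline as covariate: variance (1 − r²)s²
- ratio: (1 + r)/2

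The article does not say whether SD 15 belongs to a single reading or to the change, so both are shown. Power is for 112 per arm, change score → baseline-adjusted.

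| r | Variance ratio | SD 15 of a single reading | SD 15 of the change |
|---|---|---|---|
| 0.3 | 0.65 | 62% → 81% | 77% → 92% |
| 0.5 | 0.75 | 77% → 88% | 77% → 88% |
| 0.7 | 0.85 | 94% → 97% | 77% → 83% |
| 0.8 | 0.90 | 99% → 99% | 77% → 81% |

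The gain shrinks as r rises. All these power figures ignore clustering and are therefore optimistic.

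**Step 3: the same ratio with between-complex variance.** There are 112 / 2 = 56 completers per complex. Assume that adjusting for individual baseline does not reduce the between-complex part. The ratio is then [(1 − ICC)(1 + r)/2 / 56 + ICC] / [(1 − ICC)/56 + ICC].
- ICC 0.02, r = 0.5: (0.98 × 0.75/56 + 0.02) / (0.98/56 + 0.02) = 0.0331/0.0375 = 0.88
- ICC 0.05, r = 0.7: (0.95 × 0.85/56 + 0.05) / (0.95/56 + 0.05) = 0.0644/0.0670 = 0.96

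The saving falls from 15–25% to about 4–12%.

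**Step 4: data dependence.** This was simulated under the null with 20,000 runs, 112 per arm, no clustering, and ANCOVA on baseline pressure as the adjusted analysis. Values are for r = 0.3, 0.5, 0.7.
- Either analysis fixed in advance: about 5%.
- Strict rule, adjusting only if baseline pressure differs at p < 0.05: 4.1%, 4.3%, 4.8%.
- Free choice of whichever result rejects: 7.7%, 7.3%, 7.0%.
- Among runs with baseline pressure different at p < 0.05: the change score rejected in 25%, 17%, 13%; ANCOVA in about 5–6%.

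**Step 5: how often the trigger could fire.** The article lists seven kinds of characteristic to compare. With one independent 5% test each, the chance of at least one difference by luck is 1 − 0.95⁷ = 0.30.

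**The case against.** The strongest defence is that the change score is a valid analysis under randomisation and already uses baseline pressure each time. This stands: preferring a covariate is a matter of efficiency and of robustness to chance imbalance, not the correction of a biased estimator. A reader might infer from the article that baseline pressure is ignored unless the trigger fires; the definition of the outcome as a change rules that out.

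It is also fair to say that covariates are evidently intended and that MANOVA may be loose naming for MANCOVA, which does give adjusted coefficients for each outcome. Even so, the trigger still has no criterion.

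Other tempting inferences go further than the article:
- **That type I error is necessarily inflated.** A strict trigger does not inflate it. The 7–8% needs a free choice, which the wording permits but does not announce.
- **That MANOVA would discard 96 of 320 participants.** That is the assumed dropout itself (0.30 × 320). It becomes an upper bound on the loss only if one MANOVA pools both visits. The article does not say so, and systolic and diastolic pressure at one visit come from the same readings.
- **That within-arm significance will be presented as a treatment effect.** The article does not say this. Nor does it set an enrolment pressure threshold that would make strong regression to the mean certain, since entry is by prior diagnosis.

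**Conclusion.** The point holds as a defect in a stated rule. The primary blood pressure analysis is not uniquely fixed before the data are seen, and the fallback named for adjustment does not in itself adjust.

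Its size depends on assumptions. If the analyst may choose freely, type I error is about 7–8% instead of 5% in an individual-level simulation; under a strict trigger there is no inflation. The variance saved by always adjusting for baseline is 15–25% for independent participants at r = 0.5–0.7, and about 4–12% at ICC 0.02–0.05 with 56 completers per complex. Neither r nor the ICC is in the article.

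A reader might infer that baseline adjustment would rescue the trial's power. It would not: the sample size and the stated tests ignore clustering, and that separate problem remains.

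**What to change.** In Data management and analysis:

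1. Delete the conditional adjustment and the MANOVA.
2. For systolic and for diastolic pressure, pre-specify one model of follow-up pressure at six and twelve months on arm, visit and arm-by-visit. Always include baseline pressure and a short fixed covariate list (for example age, sex and antihypertensive treatment at baseline). Use all available visits, so that a participant seen only at six months still contributes.
3. Name the adjusted between-arm difference in mmHg with its 95% CI as the primary result.
4. Show within-arm changes descriptively, without tests.
5. Handle complex by a random effect or a cluster-level analysis with small-sample inference: four complexes less two arms leaves about 2 degrees of freedom (t critical value 4.30). A fixed effect for complex is collinear with arm and cannot be used.

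**Cost.** Items 1–4 change wording only; baseline pressure is already measured, and adding it as a covariate has no real downside. Item 5 has a price: the confidence interval widens, because it then reflects how few complexes were randomised.

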## Ethical consideration

Ethical approval was obtained from the Medical Ethics Committee, University Malaya Medical Centre (Reference Number: 944.18). The trial was registered at Iranian Clinical Trial registry (Reference Number: IRCT2013030512705N1). The control groups will be receiving all components of intervention after completion of the study.

## Discussion

Hypertension is a major contributor to the growing global pandemic of cardiovascular diseases and stroke. It is also one of the main non communicable diseases in Malaysia that are becoming an economic burden of the nation [30]. By realising the health need of the nation, the Malaysian Ministry of Health adopted the National Strategic Plan for Non-Communicable Disease (NSPNCD) in 2010 [31]. The NSPNCD aimed to achieve health promotion and prevention of NCD by increasing awareness of risk factors and adopting a healthy lifestyle in community based approach.

Our intervention is in line with national strategy and approach for prevention and control of hypertension. Previous studies showed that adherence to the "Dietary Approaches to Stop Hypertension (DASH) diet" alone can reduce both systolic and diastolic blood pressure [7,18]. Our lifestyle modification incorporates peer support self-blood pressure monitoring and training for home-based exercise to enhance the effect on blood pressure control. Several previous studies conducted in high income countries used either fixed or mobile phone as a method of delivering health coaching either via phone call or short message [10,32-34]. We selected face to face health coaching and exercise training as an appropriate approach since the education status and functional health literacy is low in our study population. Providing an exercise CD and BMI calculator would also motivate and assist our participants to engage in home-based exercise.

We selected a low income urban community as population of interest in order to reduce existing disparities in health status and access to health care across population sub-groups. Previous research conducted in the study area showed that prevalence of hypertension and other cardiovascular risk factors are higher compared to the nation-wide study. The health system in Malaysia is heavily financed by the Government and all citizens can enjoy financial and geographical access to health care [35]. However, there were several undiagnosed cases of hypertension due to lack of awareness of disease symptoms and irregular medical check-up [3]. In addition, poor treatment adherence and non-compliance behaviour challenged effective hypertension control since many people were unaware of the serious complications of hypertension. A previous study conducted in Malaysia showed that more than 95% of patients were unaware that hypertension requires long term treatment [36].

One of the expert recommendations to improve hypertension management in Asia is to increase awareness of hypertension, enhance treatment adherence and promote home blood pressure monitoring [4]. Positive impact of self-monitoring of blood pressure on treatment adherence and reduction of blood pressure has been demonstrated in high income countries [11,13,37,38].

However, to obtain a blood pressure monitor is a big challenge since more than half of our study population have an average household income less than 2,000 MYR which equivalent to (USD 605). The purchase of a reliable quality digital blood pressure monitor would cost about 10% of household income which is generally considered as catastrophic health care expenditure [39]. Our study proposed a solution to overcome the issue of unaffordability to obtain the blood pressure monitor. Since there is an existing social network in the community and practice of sharing resources, we formed a peer support group and provided a digital blood pressure monitor. We believed that it would encourage the sharing of knowledge on hypertension, disease progress and practice of self-blood pressure monitoring among the participants. Although it is expensive for a single person to purchase a blood pressure monitor for his/her own, sharing equipment among peer group members would be affordable and a practical solution for a low income community who lives the same community housing complex.

We expected that after completing intervention, the participants of our study could benefit by increasing awareness of healthy diet and physical activity, adopting healthy life style and improving self-management of hypertension. The proposed intervention would ensure the self-efficacy and self-regulation of regular blood pressure monitoring, healthy diet choice, and maintaining physical activities and exercise with peer social support. There would be a promising possibility that our intervention is widely replicable and adopted as a model of community based approach for combating hypertension in low and middle income countries.
